Results from the trial will be reported according to the CONSORT extension for stepped wedge cluster randomised designs. LGA and patient demographics will be described by LGA and period. All available primary and secondary outcomes will be analysed at the patient level using mixed-effects logistic regression models with a random intercept for cluster and fixed effects for each period and for the intervention. The Kenward-Roger correction will be applied to adjust for the small number of LGAs. Since there may be imbalance between the LGAs with respect to various baseline characteristics, in a secondary analysis we will adjust for potential confounders known to influence ambulance use that are available in the VEMD (e.g. age, sex, Australian born). Estimated effects will be expressed as odds ratios and as risk differences, with 95% confidence intervals. A secondary analysis will include an interaction between time and treatment to investigate a cumulative effect of the intervention over time. It has been shown that misspecification of the within-cluster correlation structure can lead to confidence intervals of incorrect widths, so sensitivity analyses allowing for more complex within-cluster correlation structures will be considered. Analyses will be conducted in Stata and/or SAS as appropriate.

We will also perform subgroup analyses (e.g. age, sex, country of birth) across the primary and secondary outcomes.

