## 2.8 Sample size

The stepped wedge design in the schematic (a six-sequence stepped wedge design, with an implementation period and two clusters assigned to the first and last sequences) will give 80% power to detect a change in the proportion of ACS patients in the eight LGAs arriving via EMS by 11%[10, 12] from a baseline of 61% to 72%, with a two-sided significance level of 5%. This detectable difference depends on an average of 40 ACS patients admitted per LGA in each two-month period (i.e. a total of 2240 ACS patients) and on the intra-cluster correlation, estimated to be 0.09 using data from the Victorian Emergency Minimum Dataset (VEMD) (2011-2015). This data indicated that more complex correlation structures, with decaying correlations over time, were unnecessary. The Stepped Wedge Stata Program was used for the sample size calculation,[13] verified using the Shiny CRT app.[14] No adjustment was made for LGA or participant attrition, as health services routinely collect the outcomes.

A sample size calculation was also conducted for two online surveys to determine a change in the level of knowledge of ACS symptoms. An online survey in 2020,[7] showed 25% of adults in the intervention LGAs (20% state-wide) could not name any heart attack symptoms. To detect a change from 25% to 10%, with 80% power and 2-sided significance level, requires a survey of 72 adults in each LGA in months 1-2 and again in months 9-10, assuming an intracluster correlation of 0.1, and a cluster autocorrelation of 0.9.

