### **3.7.1 Main analysis**

Both a relative risk and an absolute risk difference will be estimated.

The absolute risk difference in arrival at hospital via EMS will be estimated by fitting a mixed-effects regression model with a binomial distribution and an identity link function, and random intercepts for local government areas and fixed effects for each period and for the intervention. The Kenward-Roger correction will be applied to adjust for the small number of local government areas.[16] Results will be presented as a risk difference and 95% confidence interval. In addition, an odds ratio will be estimated by fitting a marginal logistic regression model (including terms for period and the intervention) via generalized estimating equations with an independent working correlation structure with the Kauermann and Carroll correction applied to the standard errors, as recommended by Thompson et al.[17]

In the case of non-convergence of the model with an identity link, estimates will be based on the marginal logistic regression model only.

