### **3.8.3 Number of Heart Health Checks**

The difference in rates of heart health checks between groups will be estimated by fitting a marginal Poisson regression model via generalized estimating equations with an offset term for the number of adults eligible for Medicare in each LGA, with an independent working correlation structure and Kauermann and Carroll

standard errors. In addition to the term for intervention condition, terms for study period will also be included in the model.

**3.8.4 *Rates of emergency department presentations for acute coronary syndrome; rates of emergency department presentations for unspecified chest pain; calls to EMS for non-chest pain; rates of out-of-hospital cardiac arrests.***

The difference in rates of emergency department presentations for ACS and unspecified chest pain, rates of out-of-hospital cardiac arrests and counts of calls between groups will be estimated by fitting a marginal Poisson regression model via generalized estimating equations with an offset term for the population size of each LGA, with an independent working correlation structure and Kauermann and Carroll standard errors. In addition to the term for intervention condition, terms for study period will also be included in the model; such terms will incorporate adjustment for seasonality.

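### The independence GEE makes no within-LGA comparison, so the primary fallback would have about 17% power and the five rate outcomes have no analysis that uses an LGA's own baseline

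*Supplement*

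**What the plan says.** SAP 3.7.1 plans two models for arrival by EMS. The risk difference comes from a binomial identity-link mixed model with LGA random intercepts, period effects and a Kenward-Roger correction. The odds ratio comes from a "marginal logistic regression model (including terms for period and the intervention) via generalized estimating equations with an independent working correlation structure", with Kauermann-Carroll standard errors. The section then adds: "In the case of non-convergence of the model with an identity link, estimates will be based on the marginal logistic regression model only".

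Sections 3.8.2 and 3.8.5 apply 3.7.1 to the binary secondary and survey outcomes. Section 3.8.4 analyses ED presentations for ACS and for unspecified chest pain, non-chest-pain calls and OHCA by Poisson GEE "with an offset term for the population size of each LGA, with an independent working correlation structure and Kauermann and Carroll standard errors". Section 3.8.3 does the same for Heart Health Checks with a Medicare-eligible offset. The stated terms in both are intervention and study period, with no LGA term.

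The latest protocol, under statistical methods, planned "mixed-effects logistic regression models with a random intercept for cluster and fixed effects for each period and for the intervention". SAP 2.8 says the design "will give 80% power to detect a change in the proportion of ACS patients in the eight LGAs arriving via EMS by 11" percentage points, from 61%, with ICC 0.09 and "an average of 40 ACS patients admitted per LGA in each two-month period (i.e. a total of 2240 ACS patients").

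**The concern.** A stepped wedge gets most of its information from each LGA's change from its own control periods. A model with period terms, no LGA term and independence weights cannot use that change. It only compares LGAs under intervention with LGAs under control within the same period.

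Two things are at stake. If the identity link fails, the primary conclusion would rest on an estimate with far less power than the trial was sized for, and the block-exchangeable check in 3.7.2 would not help because it repeats only the risk-difference model. For the five rates there is no second model at all. Their rate ratios would depend on how Greater Bendigo and Campaspe happened to differ from Whittlesea and Hume before the campaign.

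**Working it through.** **Layout.** From SAP Table 1 and protocol Table 4, with transition cells removed (SAP 3.2), intervention/control cells by period are:

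| T1 | T2 | T3 | T4 | T5 | T6 | T7 | T8 |
|---|---|---|---|---|---|---|---|
| 0/8 | 0/6 | 2/5 | 3/4 | 4/3 | 5/2 | 6/0 | 8/0 |

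That is 56 cells; 56 × 40 = 2,240, the plan's total.

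**The plan's own figure.** Inputs from SAP 2.8: 61% baseline, 11-point effect, ICC 0.09, 40 per cell, two-sided 5%. With variance σ² = 0.61 × 0.39 = 0.2379, a random LGA intercept and fixed periods, the generalised least squares SE is 0.0396. Power = Φ(0.11/0.0396 − 1.96) = 79.4%. Other variance conventions give 81.9% and 82.4%. So the stated 80% assumes an analysis that uses within-LGA change.

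**Weights under independence (linear scale).** Let n1 and n0 be the intervention and control cells in a period, and S = Σ n1·n0/(n1+n0) = (10+12+12+10)/7 = 44/7. An intervention cell has weight [n0/(n1+n0)]/S and a control cell −[n1/(n1+n0)]/S. Where n1 or n0 is zero the weight is exactly zero: 8+6+6+8 = 28 cells. In the logistic model, refitting to T3-T6 alone returned the identical log odds ratio (0.4587).

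Net weights by LGA:
- Bendigo and Campaspe: +14/44 = +0.32 each
- Maribyrnong: +9/44 = +0.20
- Wodonga: +3/44 = +0.07
- Warrnambool: −0.07
- Mildura: −0.20
- Whittlesea and Hume: −0.32 each

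Under the random-intercept model no net weight exceeds 0.02 in size.

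**Variance under independence.** Var = (Σ net weight²)·ρσ² + (1/S)·(1−ρ)σ²/40.
- Σ net weight² = (4×196 + 2×81 + 2×9)/1936 = 0.498, and 1/S = 0.159.
- Between-LGA part: 0.498 × 0.09 × 0.2379 = 0.01066.
- Within-LGA part: 0.159 × 0.91 × 0.2379/40 = 0.00086.
- SE = √0.01152 = 0.107, so the variance is 7.4 times that of the random-intercept model.
- Power = Φ(0.11/0.107 − 1.96) = 17%. Detectable difference = 2.80 × 0.107 = 30 points.

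| ICC | Random intercept | Independence |
|---|---|---|
| 0.01 | 83% | 67% |
| 0.02 | 80% | 48% |
| 0.05 | 79% | 26% |
| 0.09 | 79% | 17% |
| 0.15 | 82% | 12% |

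Simulated binary trials on the odds-ratio scale agree: the SD of the log OR was 0.47, against 0.20 with LGA terms, and power was 17% against 70%. With unequal LGA sizes (assumed sets) power was about 15%, against 76% to 78% for the random-intercept model.

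**Rates, precision.** The documents give no between-LGA variation for rates. Assuming an SD of the log rate of 0.1 to 0.5 and 40 to 1,000 events per equal cell, the detectable rate ratio is 1.2 to 2.7 as planned and 1.05 to 1.27 with LGA fixed effects.

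**Rates, illustration of imbalance only.** The protocol gives 1,635 ACS events a year, 102 to 360 per LGA, and residents by unnamed row. Assume its rows follow the order of SAP Table 2. Assume also Whittlesea and Hume 360 each; Campaspe, Wodonga and Warrnambool 102 each; and the remaining 609 split in proportion to residents (Greater Bendigo 269.3, Maribyrnong 208.6, Mildura 131.1). With no intervention effect, the intervention-to-control rate ratios by period are:
- T3: (371.3/149,862)/(1,055.1/542,512) = 1.27
- T4: (579.9/236,804)/(953.1/502,412) = 1.29
- T5: (681.9/276,904)/(851.1/468,757) = 1.36
- T6: (783.9/310,559)/(720/414,099) = 1.45

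The planned Poisson model pools these to about 1.3 (1.35). With LGA effects it returns 1.00.

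**The case against.** **The planned primary analysis is sound.** This stands. The hypotheses in SAP 2.7 concern the risk difference, the mixed model for it matches the power basis, and Table 5 gives no p-value for the primary odds ratio. A reader might infer that the trial's primary analysis has 17% power. It does not: that figure applies only if the identity-link model fails, and the documents give no probability for that. The binary secondary and survey outcomes likewise keep a mixed-model risk difference unless their own model fails.

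**Randomisation protects the estimate.** This also stands. A reader might call the odds ratios and rate ratios confounded. LGAs were randomised to sequence, so the independence estimator is not systematically biased, and the robust SE is meant to reflect between-LGA spread. What is left is imprecision and chance imbalance in one realised allocation of six units (two pairs and four single LGAs). In that allocation one pair is always treated and the other always control throughout T3-T6.

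**The size of the rate imbalance is unknown.** Agreed. A reader might assume one common rate in the other six LGAs, which gives 1.37. But that implies about 84, 94 and 100 events in Warrnambool, Campaspe and Wodonga, all below the stated minimum of 102. Other splits within the stated total and range gave null rate ratios from about 0.77 to above 5. Protocol Table 1 also counts all residents (779,316), whereas the SAP specifies adults, and SAP 2.2 and the protocol's consent section cite 1.8 million. The other four rates have no baseline figures at all.

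**The method is cited as recommended.** The SAP relies on a simulation study of small-sample corrections, which could not be consulted. A corrected SE can make an interval valid, but it cannot restore information that the weights discard. The alternative has limits too: in simulation, exchangeable weights gave 59% to 77% power depending on the reference distribution, against 14% to 24% with independence.

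**The protocol's model was different.** A change between documents is not a fault in itself, and none is claimed.

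**Conclusion.** The concern holds in a limited form. That half of the analysed LGA-periods get zero weight is exact for this schematic and needs no assumption beyond the stated model terms. The loss of power in the fallback is large at the plan's own inputs (17% against 79%) and present at every ICC from 0.01 to 0.15. The 17% assumes equal cells of 40, a constant within-LGA correlation and a normal reference. With cluster autocorrelation of 0.8 to 0.9 (and a slightly smaller variance convention) the comparison is 20% to 21% against 59% to 69%.

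The certain consequence falls on the five rate outcomes, which have no within-LGA analysis. The consequence for the primary outcome is conditional on non-convergence. The direction and size of any imbalance in the rates cannot be read from the documents, and the 1.3 is illustrative. Severity: should be fixed.

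**What to change.** - **3.8.3 and 3.8.4:** add LGA fixed effects, or an LGA random intercept, to the Poisson models.
- **3.7.1, fallback:** replace the final sentence so that non-convergence leads to a model that keeps within-LGA information. Either the protocol's random-intercept logistic model or a GEE with exchangeable working correlation, small-sample-corrected SEs and a named t reference would serve.
- **3.7.1 and 3.8.2, companion odds ratios:** use the same model.
- **Independence GEE:** keep it as a sensitivity analysis, described as a between-LGA comparison within T3-T6.

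The cost is SAP wording and a few lines of code, with no new data. There are small downsides. A working correlation must be estimated from eight LGAs, or the odds ratio becomes conditional on LGA. With LGA fixed effects the leverage matrix in the Kauermann-Carroll correction is singular, so the SAP should say how the SE is then computed or choose the random intercept.

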### **3.7.2 Different within-cluster correlation structures**

To assess the impact of the assumption of different within-cluster correlation structures on the estimation of the effect of the education campaign on the primary outcome, the analysis estimating a risk difference in Section 3.7.1 will be repeated assuming a block-exchangeable within-cluster correlation structure, including random effects for cluster and cluster-period.

### **3.7.3 Adjusted analyses**

Since there may be imbalances between the LGAs with respect to various patient-level baseline characteristics, the analyses described in Section 3.7.1 will be repeated including patient characteristics that are known to influence EMS use that are available in the VEMD: age, sex, Australian-born, interpreter required, living arrangements, and ACS sub-type.[10] In the case of non-convergence or collinearity, covariates may be examined for collinearity and sequentially removed from the model until convergence is achieved.

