#### **3.1.2 Level of statistical significance**

All applicable statistical tests will be 2-sided and will be performed using a 5% significance level. No adjustments for multiplicity will be made. Instead, 95% confidence intervals and p-values will be reported.

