## 5 Proposed outputs

### 5.1 Tables

**Table 1. Number of acute coronary syndrome patients arriving at emergency departments via EMS and total number of acute coronary syndrome patients arriving at emergency departments by LGA and period**

|       | Dec/Jan | Feb/Mar | Apr/May | Jun/Jul | Aug/Sep | Oct/Nov | Dec/Jan | Feb/Mar | Total   |
|-------|---------|---------|---------|---------|---------|---------|---------|---------|---------|
| LGA 1 | n/N (%) |         | n/N (%) | n/N (%) | n/N (%) | n/N (%) | n/N (%) | n/N (%) | n/N (%) |
| LGA 2 | n/N (%) |         | n/N (%) | n/N (%) | n/N (%) | n/N (%) | n/N (%) | n/N (%) | n/N (%) |
| LGA 3 | n/N (%) | n/N (%) |         | n/N (%) | n/N (%) | n/N (%) | n/N (%) | n/N (%) | n/N (%) |
| LGA 4 | n/N (%) | n/N (%) | n/N (%) |         | n/N (%) | n/N (%) | n/N (%) | n/N (%) | n/N (%) |
| LGA 5 | n/N (%) | n/N (%) | n/N (%) | n/N (%) |         | n/N (%) | n/N (%) | n/N (%) | n/N (%) |
| LGA 6 | n/N (%) | n/N (%) | n/N (%) | n/N (%) | n/N (%) |         | n/N (%) | n/N (%) | n/N (%) |
| LGA 7 | n/N (%) | n/N (%) | n/N (%) | n/N (%) | n/N (%) | n/N (%) |         | n/N (%) | n/N (%) |
| LGA 8 | n/N (%) | n/N (%) | n/N (%) | n/N (%) | n/N (%) | n/N (%) |         | n/N (%) | n/N (%) |
| Total | n/N (%) | n/N (%) | n/N (%) | n/N (%) | n/N (%) | n/N (%) | n/N (%) | n/N (%) | n/N (%) |

n=number of acute coronary syndrome patients arriving at emergency departments via EMS emergency medical services in that LGA in that period; N= total number of acute coronary syndrome patients arriving at emergency departments via emergency medical services EMS in that LGA in that period. Yellow cells = control periods; blue cells = Heart Matters intervention periods; black cells = transition periods. Data from transition periods will not be analysed.

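### SAP 3.7.3 drops covariates until the adjusted identity-link model converges; at the planned ICC and effect, fitted risks above 1 would often trigger this, so the adjusted risk difference may not use the prespecified set

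*Supplement*

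**What the plan says.** SAP 3.7.1 estimates the risk difference by "fitting a mixed-effects regression model with a binomial distribution and an identity link function", with random LGA intercepts and fixed effects for period and intervention. A marginal logistic model, fitted by generalised estimating equations (GEE) with Kauermann-Carroll standard errors, gives the odds ratio. If the identity-link model does not converge, 3.7.1 relies on the logistic model alone.

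SAP 3.7.3 repeats these analyses with age, sex, Australian birth, need for an interpreter, living arrangements and ACS sub-type, chosen because they are known to influence EMS use. Its rule for trouble differs from that in 3.7.1: "covariates may be examined for collinearity and sequentially removed from the model until convergence is achieved". It gives no order, no collinearity threshold, no minimum set and no duty to report what was dropped. It does not say whether the risk-difference and odds-ratio models must keep the same covariates, or whether the 3.7.1 fallback also applies.

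SAP Table 7 puts the adjusted risk difference and adjusted odds ratio on adjacent lines, with no entry for the covariates retained.

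**The concern.** An identity-link binomial model needs every fitted risk to lie between 0 and 1. Adding covariates spreads the fitted risks, and in an LGA with high EMS use under the intervention there may be little room left. This is a separate cause of failure from collinearity. Inspecting covariates for collinearity will not find it, and the only action the rule then offers is to remove covariates.

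The adjustment set would then be settled after seeing the data, by numerical behaviour rather than by relevance to EMS use. The logistic model has no such range limit, so the two adjusted estimates in Table 7 could be adjusted for different covariates without the reader knowing. A larger true effect pushes fitted risks closer to 1, so the problem is more likely in the very case where the intervention works.

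**Working it through.** **Inputs from the SAP.** Section 2.8 gives "a six-sequence stepped wedge design, with an implementation period and two clusters assigned to the first and last sequences", 61% to 72%, 40 patients per LGA per two-month period, 2,240 in total, ICC 0.09, 80% power and two-sided 5%. The note to Table 1 in 5.1 adds: "Data from transition periods will not be analysed". That leaves 7 analysed periods per LGA, and 8 × 7 × 40 = 2,240.

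**The plan's own figure reproduces.** Generalised least squares was used with fixed periods. The covariance of an LGA's seven period means is σ²(1 − 0.09)/40 on the diagonal plus σ² × 0.09 throughout. With σ² at the mean proportion, 0.665 × 0.335 = 0.2228, the standard error is 0.0383. Power = Φ(0.11/0.0383 − 1.96) = Φ(0.91) = 82%. With the control variance, 0.61 × 0.39 = 0.2379, it is 79%. The stated 80% is sound, so the same inputs are used below.

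**Room below 1.**
- Between-LGA SD on the risk scale = √(0.09 × 0.61 × 0.39) = 0.146.
- If LGA risks are normal, the highest of eight is expected about 1.42 SD above the mean.
- Under the intervention that LGA sits at about 0.72 + 1.42 × 0.146 = 0.93.
- About 7 percentage points remain for the combined upward effect of six covariates.

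**Simulation.** Datasets followed the design above with no secular trend: 400 per scenario with LGA risks drawn on the risk scale, and 500 with a logit truth (LGA SD 0.67 logits, matched to ICC 0.09). The identity-link binomial likelihood with LGA intercepts was maximised with the LGA variance held at its true value. Failure means that the maximum puts some fitted risk outside (0,1).

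The following are assumptions, not figures from the documents:
- Prevalences: age 45–64 37%, 65+ 55%, female 35%, Australian-born 65%, interpreter 8%, lives alone 25%, acute myocardial infarction 70%.
- Largest covariate risk difference: 0 (none), 0.05 (weak), 0.10 (moderate), 0.18 (strong).
- Largest odds ratio in the logit runs: 1.0, 1.25, 1.6, 2.3.

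Failure of the full adjusted model at ICC 0.09:

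| LGA risks, true effect | None | Weak | Moderate | Strong |
|---|---|---|---|---|
| Normal, 11 points | 49% | 65% | 86% | 98% |
| Beta, 11 points | 46% | 57% | 85% | 98% |
| Logit-normal, 61% to 72% | 21% | 32% | 63% | 91% |
| Normal, no effect | 16% | 26% | 44% | 86% |
| Logit-normal, no effect (250 datasets) | 6% | 9% | 32% | 76% |

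- **Without covariates**, at the planned effect, the identity-link model failed in 1–3% (logit) or 7–32% (normal or beta) of datasets. In the logit runs the full model failed while the covariate-free model fitted in 19–90%.
- **ICC.** With normal LGA risks, the planned effect and weak to moderate covariates, failure was 37–67% at ICC 0.05 and 1–9% at ICC 0.01.
- **Fixed LGA terms.** A separate logit-truth run of 200 datasets, with its own assumed covariates, gave 46% (weak) and 92% (moderate), against 2–3% with none.

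**How far removal would go.** Sequential removal was run with moderate covariates at ICC 0.09 and the planned effect, where the full model failed in 81–85%. A fit was reached with at most two of the six removed in 53% (random order) to 77% (strongest first) of datasets, counting those that needed no removal. Five or more had to go, or no model fitted, in 15% and 8% respectively. With weak covariates the latter figure was 7–8%.

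**The case against.** The best counter-argument is that no failure rate follows from the plan alone. ICC 0.09 and 61% to 72% are stated, but covariate effects, prevalences and the shape of the LGA distribution are not. A reader might infer that the planned ICC and effect by themselves imply failure in half to nine-tenths of datasets. The documents do not support that: changing the assumptions moves the rate from about 20% to 98%, and a smaller realised ICC or effect lowers it. Failure here also means that no solution exists inside (0,1). The SAP's trigger is non-convergence or collinearity, and software may stop, warn or return a boundary fit. These limits on the size stand.

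A reader might also infer that the adjusted risk difference would end up adjusted for little or nothing. The removal runs put that outcome in the tail, at about 7–15%. Nor does the SAP say that the strongest predictors go first or that the two models will keep different sets. It leaves both open, so these are possibilities, not predictions.

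Finally, the analysis is supporting: the protocol's statistical methods section calls adjustment a secondary analysis. The adjusted odds ratio has no range limit, and the 3.7.1 fallback could be read as carrying over, since 3.7.3 repeats the 3.7.1 analyses. That reading is available, but 3.7.3 writes its own, different rule and does not say which prevails. If the covariate-free model fails too, removal never reaches convergence, and 3.7.3 names no end point.

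**Conclusion.** The concern holds. SAP 3.7.3 turns a named adjustment set into one that can be altered after seeing the data, in no stated order. At the planned ICC and effect, fitted risks above 1 would be a frequent reason for using the rule: roughly 20–98% of simulated datasets, conditional on the assumptions listed and on how the software treats boundary fits. In each covariate scenario failure was more frequent with the planned effect than with none (for example 63% against 32% for moderate covariates under a logit truth). The likely consequence is an adjusted risk difference that has lost some covariates and may not match the adjusted odds ratio beside it; losing nearly all would be uncommon. The unadjusted main result does not depend on this rule. The change is worth making because a better method is available and cheap.

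**What to change.** In SAP 3.7.3:

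1. For non-convergence, replace removal with one prespecified fallback that keeps all six covariates. Choose one now:
   - a standardised risk difference from the adjusted marginal logistic model (mean predicted risk over the analysed patients with intervention set to on, minus the mean with it set to off), with a small-sample-corrected interval such as the delta method applied to the Kauermann-Carroll variance; or
   - a Gaussian linear mixed model with Kenward-Roger, as SAP 3.8.5 already uses for the survey counts.
2. Define failure to include a boundary fit or any fitted risk outside (0,1), so that the trigger does not depend on the program used.
3. Use the same covariates for the adjusted risk difference and the adjusted odds ratio.
4. Keep removal only for true collinearity, in a fixed order, applied to both models, and reported in a footnote to Table 7.

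The cost is a few sentences in the SAP and slightly more analysis work, mainly the corrected interval if standardisation is chosen. No new data are needed.
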